### Psychological assessments during the experiment

During each experimental session, i.e., before, during, and after completion of the Trier Social Stress Test (TSST), further electronic assessments of psychological variables will take place.

#### Rumination

Changes in ruminative thinking will be assessed repeatedly before and after completion of the TSST (i.e., at − 1 as well as + 20 min relative to the TSST) using a German version of the 8-item Brief State Rumination Inventory [BSRI, 44] from Michel-Kröhler, Wessa, and Berti [45]. In this questionnaire, participants will be instructed to indicate how they feel or think in the present moment. The scale comprises eight items (e.g., “Right now, I am reflecting about my mood.”) which will be answered on a 100-mm visual analog scale ranging from “completely disagree” (0) to “completely agree” (100). Total scores will be obtained by summing up all items. The translated version of the questionnaire has not been validated yet, however, among existing state rumination measures in English the BSRI is regarded as the most established and appropriate measure for the present study.

#### Self-compassion

To capture the current level of participants’ state self-compassion during the experimental sessions, we have translated the items of the State Self-Compassion Scale Short Form (SSCS-S) from Neff et al. [46] into German, which have not been validated yet. In this questionnaire, participants will be asked to indicate how they are feeling toward themselves in the present moment. All six statements of the SSCS-S (e.g., “I’m giving myself the caring and tenderness I need.”) will be answered on a 5-point Likert scale ranging from “not at all true for me” to “very true for me”. Three items will be reverse-coded, and total means will be calculated to obtain total state self-compassion scores. To assess changes in state self-compassion over the course of each experimental session, state self-compassion will be measured repeatedly before and after completion of the TSST (i.e., at − 1 as well as + 20 min relative to the TSST).

#### Affect

Participants’ affective states will be assessed using a German version of the Positive and Negative Affect Schedule [PANAS, 47] from Krohne et al. [48]. The scale comprises 20 items which ask participants to judge how strongly they experience positive (e.g., “excited”) or negative (e.g., “angry”) emotions during a specific task or situation. Ratings will be made on a 5-point Likert scale ranging from “not at all” to “very much”, and total scores will be calculated by summing up items on each subscale. To check whether the experimental manipulations were successful on a psychological level, affect will be measured repeatedly before and after completion of the TSST (i.e., at baseline, − 1 as well as + 1, + 20, + 120 min relative to the TSST).

#### Stress appraisal

During the preparation period of the TSST, participants’ anticipatory stress appraisal will be assessed using a German version of the 16-item Primary Appraisal Secondary Appraisal (PASA) questionnaire from Gaab [49]. The questionnaire was specifically designed to assess cognitive appraisal processes and measures participants’ anticipatory appraisals of challenge (e.g., “This task challenges me.”), threat (e.g., “This situation scares me.”), self-concept of own abilities (e.g., “In this situation, I know what I can do.”), and control expectancies (e.g., “I can best protect myself from failure in this job interview through my own behavior.”). Ratings will be made on a 6-point Likert scale ranging from “strongly disagree” to “strongly agree”, and after reverse-coding five items, final scores will be computed by summing up all item scores.

In addition, participants’ experience of task-related stress will be repeatedly assessed over the course of each experimental session using a German version of the 24-item Short Stress State Questionnaire [SSSQ, 50]—a short version of the Dundee Stress State Questionnaire [DSSQ, 51] from Ringgold et al. [SSSQ-G, 52]. In this questionnaire, participants will be asked to indicate how well each adjective describes how they feel before and during the task (e.g., “dissatisfied”) and how strongly they experience positive (e.g., “excited”) or negative (e.g., “angry”) emotions before and during the TSST. Ratings will be made on a 5-point Likert scale ranging from “not at all” to “extremely”, and total scores will be calculated by summing up items on each subscale. The questionnaire will be filled out before and after completion of the TSST (i.e., at − 1 as well as + 1 min relative to the TSST).

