After arrival at the laboratory, participants will be accommodated in a comfortable armchair and receive verbal and written instructions from trained study staff. Upon providing verbal and written informed consent regarding the collection and use of their data and biological specimens, participants will be fitted with HRV sensors (Portabiles, Erlangen, Germany). They will then be asked to provide a baseline saliva sample, followed by the initial placement of a peripheral venous catheter (Vasofix Braunüle, Braun, Melsungen, Germany). After a 45-min resting period to ensure adequate recovery from either the catheter insertion or travel to the laboratory, participants will be introduced to a modified version of the original TSST procedure [54]. During this procedure, participants will be guided to a test room and introduced to a selection committee comprising one female and one male observer wearing white lab coats. Participants will be instructed to take the role of a job applicant and deliver a 5-min speech to present themselves as the best candidate for a vacant position (i.e., their “dream job”). They will receive 5 min to prepare for their talk, after which they will be instructed to stand in front of the panel and begin their speech. Once their presentation is completed, participants will be given a mental arithmetic task for additional 5 min, in which they will be asked to serially subtract 17 from 2043 as quickly as possible. In the case of any error, they will be requested to start over. The panel will remain neutral and provide no feedback throughout the entire task. Additionally, both the 5-min speech as well as the mental arithmetic task will be audio- and videotaped for further analysis. Saliva samples will be collected immediately before (–1) as well as + 1, + 10, + 20, + 30, and + 45 min after the TSST. Plasma and RNA samples will be collected immediately before (–1) as well as + 30 and + 120 min after stress exposure. Psychological assessments will be carried out before, during, and after completion of the TSST via questionnaires (see “Psychological assessments during the experiment”).

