### Outcome measures

#### Primary outcomes

Primary outcomes will include self-reported measures of affect, appraisals of task-related stress, trait and state rumination, as well as trait and state self-compassion. Further primary outcomes will be response and habituation indices of biological stress measures for HPA axis, autonomic, and inflammatory responses (i.e., cortisol, sAA, HR, HRV, plasma IL-6, cytokine expression rates of IL-6, IL-1β, NF-кB, IкB). To obtain response indices, delta scores will be computed for the initial and repeated exposure to stress using peak values relative to baseline (e.g., peak cortisol values at + 1, + 10, or + 20 min post-TSST minus cortisol values at –1 min pre-TSST). To obtain habituation indices of biological stress measures, values of the second stress response will be subtracted from the first stress response values.

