### Hypotheses

By increasing either ruminative or self-compassionate thoughts among healthy young adults, the intervention programs are expected to affect the regulation of occurring emotions as expressed by the responsiveness of biological systems during repeated stress exposure.

To check whether the experimental manipulations are successful on a psychological level, self-report measures will be assessed repeatedly over the course of each experimental session and are expected to change over the course of experimental sessions 1 and 2. Specifically, we hypothesize that stress will elicit changes in affect scores and stress appraisals, whereas the two intervention programs are expected to induce changes in affect, self-compassion and rumination, which will be stronger than in the control group (no intervention). Furthermore, we expect these variables to predict indicators of biological stress system activity.

Hypothesis 1: Independent of experimental session and group, stress will elicit significant increases of negative affect and stress appraisals as well as decreases of positive affect.Hypothesis 2: At experimental session 1, stress-induced changes of positive and negative affect and stress appraisals will be indifferent between participants from intervention groups 1 (rumination) and 2 (self-compassion) as well as participants from the control group (no intervention).Hypothesis 3: At experimental session 2, stress-induced decreases of positive affect as well as increases of negative affect and stress appraisals will be strongest in participants from intervention group 1 (rumination) and lowest in participants from intervention group 2 (self-compassion).Hypothesis 4: Increases in state self-compassion and positive affect from pre- to post-intervention will be strongest in intervention group 2 (self-compassion), and increases in state rumination and negative affect will be strongest in intervention group 1 (rumination).

Furthermore, we expect significant responses of biological stress system activity in all experimental groups at each experimental session. Specifically, we expect responses of biological stress system activity to be similar at experimental session 1 and participants from intervention group 2 (self-compassion) to show stronger habituation of stress system activity compared to intervention group 1 (rumination) or the control group (no intervention).

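### The PASA, given during TSST preparation, yields a level and not a stress-induced change; H1–H3 should name the SSSQ-G for change and adjust the session-2 PASA for session 1

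*Protocol article*

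**What the plan says.** The Stress appraisal section of the protocol article describes two questionnaires.

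- **PASA.** The section says that "anticipatory stress appraisal will be assessed using a German version of the 16-item Primary Appraisal Secondary Appraisal (PASA) questionnaire", and the timing is given as "During the preparation period of the TSST, participants’ anticipatory stress appraisal will be assessed". Its content is prospective: "The questionnaire was specifically designed to assess cognitive appraisal processes and measures participants’ anticipatory appraisals of challenge", together with threat, own abilities and control. No other PASA time point appears in the text.
- **SSSQ-G.** Here "experience of task-related stress will be repeatedly assessed over the course of each experimental session", and "The questionnaire will be filled out before and after completion of the TSST", at −1 and +1 min.

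The Hypotheses section then speaks of stress appraisals without naming either questionnaire. H1 expects that "stress will elicit significant increases of negative affect and stress appraisals as well as decreases of positive affect". H2 expects the stress-induced changes at session 1 not to differ between arms. H3 orders the increases at session 2 by arm, largest under rumination and smallest under self-compassion. The Primary outcomes section is equally general: "Primary outcomes will include self-reported measures of affect, appraisals of task-related stress".

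The Data preparation and statistical analysis section plans ANCOVAs for self-report and biological measures alike. For these group comparisons it names covariates (sex and BMI) only for the biological data.

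**The concern.** A hypothesis about a stress-induced change needs a value before the stressor and one during or after it. The PASA as described has only one of the two. The Experimental setting and procedure section shows that participants have by then met the panel and been told their role: "They will receive 5 min to prepare for their talk, after which they will be instructed to stand in front of the panel". The questionnaire is answered inside that five-minute window, so it is already a response to the announced stressor.

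The label in the hypotheses, stress appraisals, fits the PASA at least as well as it fits the SSSQ-G, because the section uses the word appraisal for the PASA and speaks of experienced task-related stress for the SSSQ-G. If the PASA were carried into H1–H3 as worded, H1 would have no change score to test on that instrument, and a difference in PASA level between arms could be described as a difference in stress-induced increase. Stress appraisal is listed among the primary outcomes, and the Randomization section states that the analyst knows group assignments and relies on the pre-registered plan to limit bias. It is therefore worth fixing which instrument answers which hypothesis.

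**Working it through.** The protocol gives no figure to reproduce on this point. The check matches assessment times to hypotheses, followed by a short precision calculation for the fix.

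**Step 1. Values available in each session, from the article's text**

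| Instrument | Before the TSST | During preparation | After the TSST | Within-session change scores |
|---|---|---|---|---|
| PASA | none stated | 1 | none stated | 0 |
| SSSQ-G | 1 (−1 min) | none stated | 1 (+1 min) | 1 |

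**Step 2. What each hypothesis needs**

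| Hypothesis | Quantity as worded | SSSQ-G | PASA |
|---|---|---|---|
| H1 | increase with stress, both sessions | available | not available |
| H2 | equal changes across arms, session 1 | available | level comparison only |
| H3 | increases ordered by arm, session 2 | available | level comparison only |

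**Step 3. What the PASA can support.** It allows a comparison of arms on level within a session, a session 1 to session 2 difference, and use as a predictor of biological responses and habituation in H9 and H10. The intervention follows the first TSST, so the session-1 PASA is a genuine pre-intervention value and the session-2 PASA a post-intervention one.

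**Step 4. Precision from using the session-1 PASA as covariate.** Let ρ be the within-arm correlation of the PASA between sessions. The documents do not give it, so 0.5 and 0.7 are assumptions. Residual variance relative to an unadjusted session-2 comparison is 1 − ρ²:

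- ρ = 0.5: 1 − 0.25 = 0.75, a reduction of 25%.
- ρ = 0.7: 1 − 0.49 = 0.51, a reduction of 49%.

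The standard error of a difference between arms scales with the square root: √0.75 ≈ 0.87 and √0.51 ≈ 0.71. The one degree of freedom spent on the covariate is negligible with 111 to 120 participants.

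**Step 5. Comparison with a simple session difference.** With equal variances in the two sessions, the difference score has relative variance 2(1 − ρ). That is 1.00 at ρ = 0.5 and 0.60 at ρ = 0.7, against 0.75 and 0.51 for ANCOVA. ANCOVA is never worse, because 2(1 − ρ) − (1 − ρ²) = (1 − ρ)² ≥ 0.

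**The case against.** The strongest reply is that H1–H3 never mention the PASA. The SSSQ-G stands under the same heading and has the before-and-after pair that the hypotheses need. The primary-outcome wording about task-related stress is also closer to the article's description of the SSSQ-G than to its description of the PASA. On that reading the SSSQ-G was always meant to supply the change. This largely stands: a reader might infer that H1–H3 on stress appraisals cannot be tested, and the article does not support that inference.

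A single anticipatory reading is also a sound use of the PASA. It asks about a task that has been announced, so it cannot sensibly be given earlier, and one value per session suffices for H9 and H10. This stands too: the timing of the PASA is not a design fault.

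A reader might further infer that comparing session-2 PASA levels confuses stable differences between people with the effect of the intervention. It does not. Allocation is randomised 1:1:1 and stratified by sex, so such differences are balanced in expectation. They add noise, and an unadjusted comparison would be unbiased.

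Finally, the assignment of instruments to hypotheses, and any covariate for self-report outcomes, may be set out in the pre-registered analysis plan, and the schedule in Table 1 is not shown. So the point cannot be that these details are missing altogether. What remains is that the article's own hypotheses use one label for two instruments, only one of which can deliver the quantity stated.

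**Conclusion.** This is a minor point that holds in a limited form. As the article describes it, the PASA measures a level of anticipatory appraisal once the stressor procedure has begun and gives no within-session change. The change wording of H1–H3 fits only the SSSQ-G, through which all three hypotheses can be tested. Nothing in the article says that a PASA level would be reported as an increase; the wording merely leaves room for it.

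The practical gain lies in the PASA part of H3. Adjusting for the session-1 PASA would leave 75% of the residual variance if the between-session correlation is 0.5, and 51% if it is 0.7. Both correlations are assumed. The gain is in precision only.

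The conclusion rests on reading the PASA as given once per session, which the text implies but the schedule table, not shown, would have to confirm.

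**What to change.** 1. In H1–H3, state that stress-induced change in stress appraisals means the SSSQ-G difference from −1 to +1 min, and name the subscale or subscales used.
2. Describe the PASA as a level outcome. Leave it out of the change statements in H1 and H2, and keep it available as a predictor in H9 and H10.
3. For the PASA part of H3, specify an ANCOVA of the session-2 PASA on arm with the session-1 PASA as covariate, and report the result as a difference in anticipatory appraisal between arms.
4. Check that the pre-registered analysis plan and Table 1 agree with this.

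The cost is rewording three hypotheses and adding one analysis sentence. Both PASA values are already planned, so no assessment, participant burden or sample size changes. The change should be made and dated before the data are analysed.

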### Biological assessments during the experiment

Main outcomes represent measures of biological stress system activity, including HPA axis and autonomic activity, which will be assessed via saliva samples and continuous electrocardiogram (ECG) recordings, as well as stress-induced responses of the inflammatory system, which will be assessed via peripheral blood samples. Table 2 provides an overview of all biological outcome measures.

**Table 2 Tab2:** Biological outcome measures

Biological outcome measure	Number of samples per session	Sampling time points per session	Sampling procedure
Autonomic nervous system			
sAA	7	Baseline, − 1, + 1, + 10, + 20, + 30, + 45 min	Saliva sample
HR	-	Continuously	ECG
HRV	-	Continuously	ECG
HPA axis			
Cortisol	7	Baseline, − 1, + 1, + 10, + 20, + 30, + 45 min	Saliva sample
Inflammatory system			
IL-6	3	− 1, + 30, + 90 min	Peripheral blood sample
IL-6 expression	3	− 1, + 30, + 90 min	Peripheral blood sample
IL-1β expression	3	− 1, + 30, + 90 min	Peripheral blood sample
NF-кB expression	3	− 1, + 30, + 90 min	Peripheral blood sample
IкB expression	3	− 1, + 30, + 90 min	Peripheral blood sample

*ECG* electrocardiogram, *HPA axis* hypothalamus-pituitary adrenal axis, *HR* heart rate, *HRV* heart rate variability, *IкB* I kappa B kinase, *IL* Interleukin, *NF-кB* nuclear Factor kappa B, *sAA* salivary alpha-amylase

To assess autonomic responses, stress-induced changes of sAA concentrations will be measured using saliva collection tubes (Salivette; Sarstedt, Nümbrecht, Germany). Furthermore, autonomic responses will be assessed via heart rate (HR) and heart rate variability (HRV) measurements (e.g., root mean square of successive differences of consecutive R–R intervals; RMSSD). To assess HPA axis activity, changes of salivary cortisol concentrations will be measured via saliva collection tubes (Salivette; Sarstedt, Nümbrecht, Germany). Peripheral immune responses to stress will be assessed by measuring changes of plasma interleukin(IL)-6 concentrations via blood sampling tubes (Monovette; Sarstedt, Nümbrecht, Germany). To determine stress-induced changes of pro- and anti-inflammatory cytokine expression rates (IL-6; IL-1β; nuclear Factor kappa B, NF-кB; I kappa B kinase, IкB), additional blood samples will be collected using tubes containing ribonucleic acid (RNA) stabilization solution (Tempus Blood RNA tube; ThermoFisher Scientific, Darmstadt, Germany).

### Experimental setting and procedure

Experimental sessions will take place on two consecutive days. On each day, participants will be scheduled between 12:30 and 15:00 to minimize the impact of circadian variations of cortisol and sAA secretion [53]. Participants will be instructed to refrain from exercising for 24 h prior to the visit, and from smoking, brushing teeth, or eating or drinking anything except water for 1 h before the visit.

After arrival at the laboratory, participants will be accommodated in a comfortable armchair and receive verbal and written instructions from trained study staff. Upon providing verbal and written informed consent regarding the collection and use of their data and biological specimens, participants will be fitted with HRV sensors (Portabiles, Erlangen, Germany). They will then be asked to provide a baseline saliva sample, followed by the initial placement of a peripheral venous catheter (Vasofix Braunüle, Braun, Melsungen, Germany). After a 45-min resting period to ensure adequate recovery from either the catheter insertion or travel to the laboratory, participants will be introduced to a modified version of the original TSST procedure [54]. During this procedure, participants will be guided to a test room and introduced to a selection committee comprising one female and one male observer wearing white lab coats. Participants will be instructed to take the role of a job applicant and deliver a 5-min speech to present themselves as the best candidate for a vacant position (i.e., their “dream job”). They will receive 5 min to prepare for their talk, after which they will be instructed to stand in front of the panel and begin their speech. Once their presentation is completed, participants will be given a mental arithmetic task for additional 5 min, in which they will be asked to serially subtract 17 from 2043 as quickly as possible. In the case of any error, they will be requested to start over. The panel will remain neutral and provide no feedback throughout the entire task. Additionally, both the 5-min speech as well as the mental arithmetic task will be audio- and videotaped for further analysis. Saliva samples will be collected immediately before (–1) as well as + 1, + 10, + 20, + 30, and + 45 min after the TSST. Plasma and RNA samples will be collected immediately before (–1) as well as + 30 and + 120 min after stress exposure. Psychological assessments will be carried out before, during, and after completion of the TSST via questionnaires (see “Psychological assessments during the experiment”).

All participants will then be randomly assigned to one of two intervention programs (intervention group 1: rumination, intervention group 2: self-compassion) or to a control condition. Participants will then receive verbal and written instructions for the upcoming task and will be asked to either engage in coping behavior (rumination vs. self-compassion) or to think neutrally about a given topic (e.g., description of everyday life) and to write down their thoughts. To check whether the experimental manipulations were successful, psychological variables will be measured repeatedly before and after each experimental condition via questionnaires (see “Psychological assessments during the experiment”). Upon completion, participants will be dismissed and reminded of the follow-up appointment (+ 1 day) and the incentive they will receive via email. With this email, participants will receive instructions to reflect on the experienced stress situation, to review and complete their notes, and to bring these notes to session 2.

The following day, participants will be scheduled at approximately the same time for experimental session 2. Procedures will closely follow those of experimental session 1, with participants being instructed to review their notes from the previous session and engage in a slightly modified version of the mental arithmetic task during the TSST (i.e., serially subtracting 13 from 2011). In contrast to experimental session 1, no further intervention will take place on this day. At the end of this session, participants will be debriefed and dismissed. To ensure quality control of the experimental procedure, regular audits will take place at intervals of 6 to 8 weeks. These audits will be conducted by a principal investigator who is independent of the data collection process. The audits will include re-training sessions for the TSST panel, as well as for staff members who interact with participants. The objective of these audits is to reinforce adherence to the protocol, address any procedural deviations, and maintain a high standard of data integrity throughout the study.

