### Experimental conditions

Figure 1 provides an overview of the allocation of participants into three experimental conditions. Participants assigned to intervention group 1 will take part in a rumination intervention, whereas participants from intervention group 2 will take part in a self-compassion intervention. Condition 3 will serve as an active control group in which participants are instructed to think neutrally about a specified topic and record their thoughts in written form.

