### Tasks and interventions

#### Intervention group 1: rumination

According to the Response Styles Theory [21], rumination is described as repetitive thought process focused on the causes, consequences, and symptoms of negative affect, which may generally cause maintenance and amplification of depressive symptoms. Furthermore, Clark and Wells [22] describe rumination that specifically occurs after psychosocially stressful events (post-event rumination) as persistent processing or reflection about a previous social interaction.

As has been revealed by previous research, rumination is generally associated with indicators of lower psychological well-being, as it predicts the occurrence of future depressive episodes [23]. Additionally, individuals who strongly ruminate about prior stressful events exhibit dysfunctional biological adaptation mechanisms, including higher cortisol responses to acute stress [24], and sustained activation of the HPA axis and the inflammatory system [25]. Preliminary work has also revealed associations between stressor-related rumination and increased stress-induced responses of HPA axis activity to repeated acute stress, suggesting that rumination may impair the habituation of biological stress system activity [14]. Due to the persistent and passive focus on negative emotions in stressful situations as well as the impaired ability to adequately biologically adapt to acute and repeated stress, rumination is thus considered to have detrimental effects on long-term health.

As demonstrated by multiple studies, rumination can be experimentally induced, which affects the activation of the HPA axis and the inflammatory system [25, 26]. An analysis with preliminary data reveals that stressor-related rumination can be induced by a short-term writing intervention which leads to a reduction of HPA axis habituation [20]. Analogous to this experimental approach, the planned study aims to manipulate rumination as coping mechanism to gain insight into whether it may lead to maladaptive biological adaptation. To this end, the first intervention is designed to experimentally induce rumination by instructing participants to ruminate about their first stress exposure and, in particular, about their negative feelings and to write down their thoughts.

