#### Control group

To ensure that any changes in stress responses are attributed to the effect of specific cognitive strategies (rumination vs. self-compassion), rather than to engaging in a thinking and writing task per se, a control group will be included in which participants will be instructed to think neutrally about a specified topic (e.g., a description of everyday life) and to write down their thoughts.

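### As written, the email between sessions tells controls as well to reflect on the stressor; this conflicts with the neutral control and biases comparisons with it in a direction that depends on the arm

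*Protocol article*

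**What the plan says.** The relevant statements are all in the Methods of the Protocol article.

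- **Control condition.** Under Experimental conditions, "participants are instructed to think neutrally about a specified topic and record their thoughts in written form". Under Control group, "a control group will be included in which participants will be instructed to think neutrally about a specified topic", with everyday life as the example. Its stated purpose is to let changes be attributed to the specific strategies "rather than to engaging in a thinking and writing task per se". The Hypotheses section labels this group as receiving no intervention.
- **Active conditions.** Under Tasks and interventions, both active arms work on the first stress exposure: one ruminates about it, the other approaches it with self-compassion. Both write their thoughts down.
- **Allocation and task.** Under Experimental setting and procedure, "All participants will then be randomly assigned to one of two intervention programs" or to control. The text then separates the arms for the session-1 task: coping behaviour for two of them, neutral thinking for the third.
- **Email.** The same paragraph continues: "With this email, participants will receive instructions to reflect on the experienced stress situation, to review and complete their notes", and to bring the notes to session 2. No arm is named or excepted.
- **Session 2.** Participants review their notes before the second stress test, again with no arm named.
- **Role of the email.** Under Risks, detailed emailed instructions are offered as a way to raise engagement with the coping strategies.

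**The concern.** The first thing the email asks for, reflection on the stress situation, does not fit the control condition. Controls wrote about a neutral topic, so their notes do not concern the stressor, yet they are told to think about it overnight. The section on the rumination intervention describes post-event rumination as "persistent processing or reflection about a previous social interaction". The stress test is a social-evaluative interaction, so the email asks controls for something close to what the rumination arm is meant to do.

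The timing makes this matter. The email acts after allocation and before the session-2 stress response. Hypothesis 7 compares that response between groups, and Hypothesis 8 compares a habituation index computed as the first response minus the second. Any shift in the control arm at session 2 therefore enters every comparison with control under both hypotheses. The trial's stated superiority aim is a comparison with control.

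**Working it through.** **1. The plan's own sample size.** Inputs from Power analysis: three groups, alpha 0.05, power 0.80, effect size printed as f² = 0.30. An omnibus F test with noncentrality λ = N·f² and f = 0.30 gives N = 111 (37 per group, power 0.803), which matches the article. Reading f² = 0.30 literally (f = 0.548) would give N = 36, so the stated N rests on f = 0.30. With 120 recruited and 10% lost, 120 × 0.9 = 108 remain, or 36 per arm.

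**2. Direction of the bias.** Hypothesis 8 orders habituation as rumination lowest and self-compassion highest, so control lies between them. The two distances from control add up to the distance between the active arms:

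(control − rumination) + (self-compassion − control) = self-compassion − rumination.

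The right-hand side does not involve the control. A shift of the control mean therefore shortens one distance and lengthens the other by the same amount.

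For illustration, take equally spaced means at the planning effect. The extreme difference is d = 0.30 × √6 = 0.735, and each distance from control is 0.735/2 = 0.367. Move control toward rumination by an assumed fraction of that distance:

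| Shift | Rumination vs control, d | Self-compassion vs control, d | Self-compassion vs rumination, d | Omnibus power, N = 111 |
|---|---|---|---|---|
| 0% | 0.37 | 0.37 | 0.735 | 0.80 |
| 25% | 0.28 | 0.46 | 0.735 | 0.81 |
| 50% | 0.18 | 0.55 | 0.735 | 0.84 |
| 100% | 0.00 | 0.73 | 0.735 | 0.91 |

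If controls drifted toward self-compassion instead, the two middle columns would swap.

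**3. Possible loss in rumination vs control.** Power analysis gives preliminary effects of d = 0.81 (cortisol) and d = 0.67 (sAA) for intervention vs control. The rumination section cites the same preliminary study for a writing task that induced rumination and reduced HPA axis habituation. It is therefore plausible, though not stated, that these values are rumination vs control effects. The documents give no figure for how far controls would follow the email, so the fraction c is assumed.

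Diluted effect: d × (1 − c). Power: two-sided two-sample noncentral t, n = 36 per arm, 70 degrees of freedom, noncentrality d·√(36/2), alpha 0.05/3 = 0.0167 (Bonferroni over three pairs).

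| c | Cortisol d | Power | sAA d | Power |
|---|---|---|---|---|
| 0 | 0.81 | 0.83 | 0.67 | 0.65 |
| 0.25 | 0.81 × 0.75 = 0.61 | 0.55 | 0.67 × 0.75 = 0.50 | 0.38 |
| 0.50 | 0.81 × 0.50 = 0.41 | 0.24 | 0.67 × 0.50 = 0.34 | 0.16 |

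**The case against.** **The article condenses the email.** One sentence summarises it, and the Risks section implies that fuller text exists, which may differ by arm. This stands as a limit: the documents show what is written, not what is sent. It does not remove the conflict, because the same paragraph separates the arms for the writing task and then stops doing so.

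**A shared prompt could be deliberate.** Both active arms think about the stressor, so prompting every arm to recall it would hold recall more constant and leave the strategy as the difference. That would be a defensible design, but the article does not state it. It also sits badly with a control described as neutral and labelled as no intervention.

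**Reflection is not rumination.** The article describes rumination as persistent and centred on negative feelings, and a single prompt need not produce that. This is fair. It bears on the size of the drift, which is unknown, more than on whether the instruction belongs in a neutral arm.

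**The self-compassion arm keeps its frame.** The same email sends these participants back to their own notes, written with self-compassion. This stands, so the point is limited to the control arm.

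**Drift would be visible.** State rumination and state self-compassion are measured 1 minute before the stress test in each session. These measures could reveal drift at session 2, but they cannot remove its effect.

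**The illustration may double-count.** If the preliminary study used a similar email, its effects already include any dilution. The documents do not say, so the power figures remain illustrative.

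**Conclusion.** The procedure section, as written, conflicts with the control condition as defined under Experimental conditions and Control group. If controls follow the email, comparisons with control at session 2 are biased. On the article's own description of rumination and its hypothesised order, the most plausible result is that rumination vs control is diluted and self-compassion vs control inflated. An apparent benefit of self-compassion could then partly reflect a worsened control.

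Three stronger readings are tempting but not supported:

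- **Every comparison with control shrinks.** With control between the other arms, a shift of its mean cannot shrink both distances.
- **The trial's results become uninterpretable.** Self-compassion vs rumination does not involve the control, and in the scenario above omnibus power does not fall.
- **Contamination is established.** The actual email text and participants' compliance with it are not shown.

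The size is unknown. The fall in power from 0.65–0.83 to 0.38–0.55 or 0.16–0.24 rests on two assumptions: that the preliminary effects are rumination vs control, and that controls take on 25% or 50% of them.

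**What to change.** Reconcile Experimental setting and procedure with Experimental conditions and Control group.

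1. Use three arm-specific emails of matched length and format. The control email asks only to review, complete and bring the notes on the neutral topic, with no instruction to reflect on the stress situation. Each intervention email repeats that arm's own instruction.
2. State that the note review at session 2 refers to each arm's own notes.
3. If the emails already differ by arm, correct the procedure section to say so; nothing else is needed.
4. If they do not, notify the ethics committee of the change in writing and flag participants who received the common email for a sensitivity analysis.

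The cost is two more email templates and a change of procedure during recruitment, which leaves two groups of participants with different email texts. Recruitment is planned to run until September 2026, so an early change keeps the first group small.
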